### **8.2.5. Guidelines for Assessing Intensity of an Adverse Device Effect**

The Investigator should use the following definitions when assessing intensity of an adverse event:

- **MILD:** Subject is aware of symptoms or has minor findings but tolerates them well, and no or minimal intervention required
- **MODERATE:** Subject experiences enough symptoms or findings to require intervention
- **SEVERE:** Subject experiences symptoms or findings that require significant medical intervention

#### **8.2.6. Guidelines for Determining Causality**

The Investigator will use the following question when assessing causality of an ADE/UADE to study device, where an affirmative answer designates the event as a suspected ADE: Is there a reasonable possibility that the device or its use caused the event? “Reasonable possibility” means that there is evidence to suggest a causal relationship between use of the device and the ADE.

#### **8.2.7. Reporting Procedures**

All recordable ADEs will be entered into the EDC within 7 days of identification. Recordable UADEs will be reported within 3 working days of identification by telephone to the Sponsor at [contact] and entered into the EDC as soon as possible thereafter.

#### **8.2.8. Anticipated Adverse Device Effects**

Due to the non-invasive nature of the devices, there are no anticipated adverse device effects directly related to IDx-DR or RV700.

The proposed study is expected to introduce only minimal risk to both the camera operators and subjects because the RV700 cameras are commercially available for ocular fundus photography and Tropicamide 1% eye drops for pupil dilation are an approved drug product used in standard care and have been demonstrated to have minimal side effects [11].

The risks associated with using these devices/products in the context of this clinical study are anticipated to be similar to those associated with the use in standard care and are provided below:

- brief discomfort due to light emitted by the fundus cameras
- brief discomfort, stinging of the eyes, sensitivity to light, or blurry vision caused by the dilation drops

#### **8.2.9. Unanticipated Adverse Device Effects**

Investigators must report any UADE to the Sponsor immediately. The Sponsor is obligated to investigate UADE reports promptly to determine reporting requirements of the event and assess if the event warrants further action by the Sponsor.

#### **8.2.10. Protocol Deviations**

A deviation is defined as an event that did not occur according to the protocol requirements. Protocol deviations will be documented on the Protocol Deviation CRF. Deviations are reported per the governing IRB requirements.

### 8.2.11. Regulatory Reporting

Any event that may be considered a UADE related to the RV700 paired with the IDx-DR device, and therefore may require reporting based on federal regulations, will be forwarded to the Sponsor for investigation. After assessing reporting requirements of the event, the Sponsor or its representative will submit reports to the FDA and other regulatory agencies as necessary and will inform the investigators of such regulatory reports. Site investigators must submit safety reports as required by their IRB. Documentation of the submission and receipt by the IRB must be retained for each safety report.

### 8.2.12. Type and Duration of Follow-up of Subjects after ADEs

ADEs/UADEs will be followed until resolved or considered stable. Adverse events will be followed by the Investigator or a qualified member of the study team. The Investigator or a qualified study team member may review the subject's medical record, contact the subject by phone, or contact the subject's primary care physician for follow-up. Subject safety data will be reviewed on an ongoing basis by the Sponsor.

## 9. Statistical Considerations

### 9.1. Hypothesis testing

In this study a minimum of 200 eyes with mtmDR and at least 140 eyes without mtmDR will be enrolled in the main diagnostic performance study. The device performance will be evaluated per eye. The primary endpoints will be sensitivity and specificity of IDx-DR paired with the RV700 in detecting mtmDR based on eye-level results when compared to a PRS by three retinal experts. Intent-to-treat (ITT) analyses are planned; supportive analyses are planned (see Statistical Analysis Plan [SAP] table shells).

As this study is intended to support an extension of the IDx-DR labeling to validate a new camera model for use with IDx-DR, the performance is expected to be substantially equivalent to the predicate device. Substantial equivalence will be assessed as non-inferiority since higher than expected performance is a favorable outcome. The non-inferiority targets will be set based on Sponsor expectations for eye-level sensitivity and specificity. Published results of this trial and NW400 subject-level estimates are summarized in [Supplementary Table 7](#)

**Supplemental Table 7:** Eye-level diagnostic design parameters and pivotal study subject-level performance

|             | Eye-level
Null Hypothesis
$p_0$ | Subject-level
Point Estimate
(two-sided 95% CI) |
|-------------|---------------------------------------|-------------------------------------------------------|
| Sensitivity | 75.0%                                 | 87.2% (81.8%-91.2%)                                   |
| Specificity | 77.5%                                 | 90.7% (88.3%-92.7%)                                   |

The study population is expected to mirror the spectrum of disease severity encountered at primary care settings, from no DR to proliferative DR (PDR), with a target sample size of at least 200 eyes (~20% of subject sample size) with more than mild DR (mtmDR+), which includes ETDRS levels 35-85, and/or clinically significant as well as center-involved macular edema as subgroup analyses. The study population is also expected to mirror the racial and ethnic distribution of the US diabetes population. Within this cohort, at least 40 eyes are expected to have vision threatening DR (vtDR), defined as ETDRS level 50-85 and/or clinically significant as well as center-involved macular edema. In addition, the same analyses will be performed at the subject-level for regulatory submission and publication, but the subject-level analyses will not have formal study hypotheses.

### 9.1.1 Sample Size, Precision, and Power

Minimum sample sizes of  $n=200$  mtmDR+ eyes and 140 mtmDR- eyes will be required. The predicate device, IDx-DR with the NW400, pivotal trial pre-specified null hypotheses for sensitivity and specificity of 75% and 77.5%, respectively; these represent pre-defined non-inferiority margins. The alternative hypotheses were 85.0% for sensitivity and 82.5% for specificity in support of a non-inferiority design. These lower thresholds for performance will be ruled out with one-sided 97.5% confidence bounds.

As this study is intended to support an extension of the IDx-DR labeling to validate a new camera for use with IDx-DR, the performance is expected to be substantially equivalent to the predicate device at the subject-level.

This study will validate the use of a new camera with the same diagnostic algorithm as currently on the market. The proposed sample size maintains a one-sided 97.5% confidence interval that exceeds the predicate device pivotal trial null hypotheses, i.e., a lower confidence limit >75% for sensitivity and >77.5% for specificity which reflects a 5% non-inferiority offset for sensitivity and a 2.5% non-inferiority offset for specificity (**Supplementary Table 8** columns 1-4). These hypothesis tests were designed specifically to reflect clinically meaningful eye-level outcomes; substantial equivalence is interpreted as non-inferiority (**Supplementary Table 8** columns 1-4).

Supplementary Table 8: Power and Significance Threshold Calculations Summary (minimum sample sizes)

---

**Digital Diagnostics Confidential.** This document is intended for internal use only and may not be disclosed or reproduced in whole, or in part, for external distribution in any form without express written permission of DDx Legal. All hard copies should be checked against the current electronic revision prior to use and destroyed promptly thereafter. All hard copies are considered uncontrolled documents.

|                                 | Sponsor Criteria (Non-inferiority) |          |             |          |
|---------------------------------|------------------------------------|----------|-------------|----------|
|                                 | Sensitivity                        |          | Specificity |          |
|                                 | Power                              | N-I      | Power       | N-I      |
|                                 | 1                           | 2 | 3    | 4 |
| Test significance level, alpha  | 0.025                              | 0.025    | 0.025       | 0.025    |
| 1 or 2 sided test?              | 1                                  | 1        | 1           | 1        |
| Null hypothesis %, $p_0$        | 75%                                | 75%      | 77.5%       | 77.5%    |
| Alternative hypothesis %, $p_A$ | 83.5%                              | 81.2%    | 87.1%       | 84.6%    |
| Power (%)                       | 80                                 | NA       | 80          | NA       |
| N                               | 200                                | 200      | 140         | 140      |

## 9.2. Demographics

Age will be summarized by eye and by subject using descriptive statistics, and sex, ethnicity, and race will be summarized using counts and percentages. Summaries will be done by diagnostic stratum and overall. Sequential enrollment versus enrichment enrollment will be summarized.

## 9.3. Endpoints

### 9.3.1. Primary Endpoint

The primary objective of this study is to estimate the sensitivity and specificity of IDx-DR with the RV700 in detecting mtmDR based on eye-level results when compared to a prognostic reference standard. For each eye from each subject enrolled, IDx-DR results will be obtained as positive for mtmDR (hereafter, positive), negative for mtmDR (negative), or exam quality insufficient/failed (ungradable). Similarly, results of positive, negative, or ungradable will be determined by the majority vote of retinal experts at a reading center as the prognostic reference standard. The unit of analysis will be the eye, and the superiority targets will be set based on expecting the point estimate for sensitivity and specificity to be the same as the observed performance of IDx-DR with the NW400 camera measured in the pivotal trial.

### 9.3.2. Secondary Endpoints

Secondary endpoints include the following:

- Sensitivity and specificity of IDx-DR using RV700 based on subject-level results against a Level I Prognostic Reference Standard (PRS)

---

**Digital Diagnostics Confidential.** This document is intended for internal use only and may not be disclosed or reproduced in whole, or in part, for external distribution in any form without express written permission of DDx Legal. All hard copies should be checked against the current electronic revision prior to use and destroyed promptly thereafter. All hard copies are considered uncontrolled documents.

- Sensitivity and specificity of IDx-DR using RV700 based on eye-level results when compared to the Wisconsin Fundus Photograph Reading Center Level II Standard grading of the RV700 images
- Sensitivity and specificity of IDx-DR using RV700 based on subject-level results when compared to the Wisconsin Fundus Photograph Reading Center Level II Standard grading of the RV700 images
- Percent of total cases where a diagnostic result can be provided by IDx-DR with the RV700
- Positive Predictive Value (PPV) and Negative Predictive Value (NPV) of IDx-DR with the RV700
- Sensitivity and specificity of IDx-DR categorizing all PRS-determined positive cases with no diagnostic result as false negatives and all PRS-determined negative cases with no diagnostic result as false positives, i.e., a “worst case scenario” analysis of the impact of “Exam Quality Insufficient” results.

### 9.3.3. Definitions for Primary and Secondary Endpoint Calculations

|               | Prognostic reference standard |           |            |           |
|---------------|-------------------------------|-----------|------------|-----------|
|               | Positive                      | Negative  | Ungradable | Total     |
| IDx-DR Result |                               |           |            |           |
| Positive      | PP                     | PN | PU  | DP |
| Negative      | NP                     | NN | NU  | DN |
| Ungradable    | UP                     | UN | UU  | DU |
| Total         | TP                     | TN | TU  | N  |

*Endpoints:*

$$\text{Sensitivity} = \frac{PP}{PP+NP}$$

$$\text{Specificity} = \frac{NN}{PN+NN}$$

$$\text{Positive Predictive Value} = \frac{PP}{PP+PN}$$

$$\text{Negative Predictive Value} = \frac{NN}{NP+NN}$$

---

**Digital Diagnostics Confidential.** This document is intended for internal use only and may not be disclosed or reproduced in whole, or in part, for external distribution in any form without express written permission of DDx Legal. All hard copies should be checked against the current electronic revision prior to use and destroyed promptly thereafter. All hard copies are considered uncontrolled documents.

$$\text{Diagnosibility} = \frac{PP+PN+NP+NN}{TP+TN}$$

*Endpoints considering ungradable eyes:*

$$\text{Sensitivity}_{+u} = \frac{PP}{PP+NP+UP}$$

$$\text{Specificity}_{+u} = \frac{NN}{PN+NN+UN}$$

$$\text{PPV}_{+u} = \frac{PP}{PP+PN+PU}$$

$$\text{NPV}_{+u} = \frac{NN}{NP+NN+NU}$$

#### 9.3.4. Analyses

A cross tabulation of IDx-DR results (positive, negative, ungradable) with the results from the reference standard (positive, negative, ungradable) will be presented for the overall sample. The point estimate for each test characteristic will be presented along with the counts of eyes (numerator and denominator) that contribute to the calculation. One-sided 97.5% confidence intervals will be computed by the cluster bootstrap approach to account for correlation introduced by taking measurements from both eyes of each subject if the confidence interval is not estimable using the cluster bootstrap approach due to small sample sizes or boundary values (e.g., a test characteristic of 100%), then the exact binomial confidence interval will be presented instead. Primary endpoints will be reported in stratified analyses by eye, age, sex, and race/ethnicity. Should enrichment be implemented, further stratification of all endpoints will be presented by cohort: sequential enrollment or enrichment.

Relevant data analyses will be repeated at the subject-level for regulatory submission and publication consistent with the de novo study utilizing the Topcon NW400 retinal camera.

Data analysis will be performed using SAS (V9.3 or later).

#### 9.4. Precision Substudy

A repeatability and reproducibility substudy will be performed including three cameras, three operators, and three replicates. The unit of analysis will be the eye (two eyes included per subject). Each of 36 subjects, 50% positive for mtmDR in at least one eye, will have a total of 9 results on each eye (see Section 9.4.1). Select subjects will be invited for the Precision Substudy based on the PRS grading of their Diagnostic Performance Study images. Eighteen (18) of the Precision Substudy subjects will have received a grade of mtmDR(+) in at least one eye, and eighteen (18) will have received a grade of mtmDR(-) in both eyes. Subjects will be fully dilated and then undergo nine IDx-DR exams. The substudy will test three RV700 cameras and three operators with three replicates using a Latin Square design.

---

**Digital Diagnostics Confidential.** This document is intended for internal use only and may not be disclosed or reproduced in whole, or in part, for external distribution in any form without express written permission of DDx Legal. All hard copies should be checked against the current electronic revision prior to use and destroyed promptly thereafter. All hard copies are considered uncontrolled documents.

The camera, operator, and replicate combinations across subjects are specified below:

Exam A: RV700 A + Operator #1 (Replicate 1)  
 Exam B: RV700 A + Operator #2 (Replicate 1)  
 Exam C: RV700 A + Operator #2 (Replicate 2)  
 Exam D: RV700 B + Operator #2 (Replicate 1)  
 Exam E: RV700 B + Operator #3 (Replicate 1)  
 Exam F: RV700 B + Operator #3 (Replicate 2)  
 Exam G: RV700 C + Operator #1 (Replicate 1)  
 Exam H: RV700 C + Operator #1 (Replicate 2)  
 Exam I: RV700 C + Operator #3 (Replicate 1)

The Latin Squares design follows where the X represents an observation and R represents a replicate in order to estimate camera effect, operator effect, and reproducibility:

|          | Operator 1 | Operator 2 | Operator 3 |
|----------|------------|------------|------------|
| Camera A | X          | X, R       | -          |
| Camera B | -          | X          | X, R       |
| Camera C | X, R       | -          | X          |

Operators will reposition subjects between each imaging replicate. The order of the data collection will be recorded in the case report form.

#### 9.4.1. Imaging Sequence for Precision Study

| Camera | Operator | Replicate |
|--------|----------|-----------|
| A      | 1        | 1         |
|        | 1        | 2         |
|        | 1        | 3         |
| B      | 2        | 1         |
|        | 2        | 2         |
|        | 2        | 3         |

---

**Digital Diagnostics Confidential.** This document is intended for internal use only and may not be disclosed or reproduced in whole, or in part, for external distribution in any form without express written permission of DDx Legal. All hard copies should be checked against the current electronic revision prior to use and destroyed promptly thereafter. All hard copies are considered uncontrolled documents.

|                      |   |    |
|----------------------|---|----|
| C                    | 3 | 1  |
|                      | 3 | 2  |
|                      | 3 | 3  |
| Total gradings / eye |   | 9  |
| Subjects per setting |   | 36 |

Endpoints for each analysis include mixed effects estimates of operator, camera, and replicate effects as well as overall agreement, average positive agreement, average negative agreement, and average ungradable agreement. Reproducibility, or inter-operator variability, will also be assessed based on agreement between three camera-operator pairs for a given subject (see Section 9.4.2). One-sided 97.5% confidence intervals for each endpoint will be computed using the clustered bootstrap approach. [12]

Data analysis will be performed using SAS (V9.3 or later).

Relevant data analyses will be repeated at the subject-level for regulatory submission and publication, consistent with the de novo study utilizing the Topcon NW400 retinal camera.

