**Supplementary Table 6: Imaging Combinations for Precision Substudy**

| Exam | Camera               | Operator | Replicate |
|------|----------------------|----------|-----------|
| A    | A                    | 1        | 1         |
| B    |                      | 2        | 1         |
| C    |                      | 2        | 2         |
| D    | B                    | 2        | 1         |
| E    |                      | 3        | 1         |
| F    |                      | 3        | 2         |
| G    | C                    | 1        | 1         |
| H    |                      | 1        | 2         |
| I    |                      | 3        | 1         |
|      | Subjects per setting |          | 9         |

Endpoints for each analysis include overall agreement, average positive agreement, average negative agreement, and average ungradable agreement. DDx algorithm repeatability, or intra-operator variability, will be assessed using mixed effects models to simultaneously estimate these three separate sources of variation (see protocol Section 9.4.2). One-sided 97.5% confidence intervals for each endpoint will be computed using the clustered bootstrap approach. [12]

Relevant data analyses will be repeated at the subject-level for regulatory submission and publication consistent with the de novo study utilizing the Topcon NW400 retinal camera.

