## 8. Criteria for Evaluation

### 8.1. Primary Efficacy Endpoint

The co-primary endpoints are the sensitivity and specificity of IDx-DR with the RV700 detecting more than mild DR (mtmDR) based on eye-level results in subjects recruited from primary care clinics when compared to a prognostic reference standard.

For secondary efficacy endpoints, the following will be analyzed:

- 1) Sensitivity and specificity of IDx-DR using RV700 based on subject-level results against a Level I Prognostic Reference Standard (PRS)
- 2) Sensitivity and specificity of IDx-DR using the RV700 based on eye-level results when compared to the Wisconsin Fundus Photograph Reading Center Level II Standard grading of the RV700 images

---

**Digital Diagnostics Confidential.** This document is intended for internal use only and may not be disclosed or reproduced in whole, or in part, for external distribution in any form without express written permission of DDx Legal. All hard copies should be checked against the current electronic revision prior to use and destroyed promptly thereafter. All hard copies are considered uncontrolled documents.

- 3) Sensitivity and specificity of IDx-DR using RV700 based on subject-level results when compared to the Wisconsin Fundus Photograph Reading Center Level II Standard grading of the RV700 images
- 4) Percent of total cases where a diagnostic result can be provided by IDx-DR with the RV700
- 5) Positive Predictive Value (PPV) and Negative Predictive Value (NPV) of IDx-DR with the RV700
- 6) Sensitivity and specificity of IDx-DR as if all PRS-determined positive cases with no diagnostic result provided were false negatives and all PRS-determined negative cases with no diagnostic results were false positives, i.e., a “worst case scenario” of the impact of “Exam Quality Insufficient” results.

For the Precision Substudy, the following will be analyzed:

- 1) Eye-level DDx algorithm score mixed model estimates of the operator, camera, sequence, dilation, and replicate effects
- 2) Average Positive Agreement (APA) in intra- and inter- configurations of RV700 cameras/operators
- 3) Average Negative Agreement (ANA) in intra- and inter- configurations of RV700 cameras/operators
- 4) Average Ungradable Agreement (AUA) in intra- and inter- configurations of RV700 cameras/operators
- 5) Overall agreement
- 6) Subject-level DDx algorithm mixed model estimates of the operator, camera, sequence, dilation, and replicate effect.

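### Replicate 2 exists only in camera-operator pairs A-2, B-3 and C-1; without a pair term, the score model puts part of any camera-by-operator interaction into the replicate effect or the residual

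*Combined protocol and SAP*

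**What the plan says.** **Layout.** Protocol 7.6 and 9.4, and SAP 3.2 and Supplementary Table 6, list nine exams (A to I) for every subject. In the grid in protocol 9.4, "X represents an observation and R represents a replicate in order to estimate camera effect, operator effect, and reproducibility". Six of the nine camera-operator cells are filled. A second replicate exists only for camera A with operator 2 (exam C), camera B with operator 3 (exam F) and camera C with operator 1 (exam H).

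**Model terms.** Three lists are in use:
- Protocol 8.1: "Eye-level DDx algorithm score mixed model estimates of the operator, camera, sequence, dilation, and replicate effects".
- Protocol 9.4.1: "Endpoints for each analysis include mixed effects estimates of operator, camera, and replicate effects".
- SAP 5.2: operator, camera, sequence, dilation and FPRC, with no replicate term. The objectives tables in SAP section 2 and protocol 3.1 match this list. SAP 5.2 nevertheless promises "mixed effects models to simultaneously estimate these three separate sources of variation".

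No list has a camera-operator term. None says whether replicate is a fixed effect or a variance component.

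**A second layout.** The table inside protocol 9.4.1 shows only pairs A-1, B-2 and C-3, with three replicates each.

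**Repeatability and order.** SAP 5.2 assesses repeatability within the replicated pairs (216 gradings) and reproducibility across the six combinations (432 gradings). Exam order is to be recorded, but the readable text prints no order.

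**The concern.** Each camera and each operator appears once among the repeated pairs (A-2, B-3, C-1) and once among the unrepeated pairs (A-1, B-2, C-3). Camera and operator main effects therefore cannot explain a difference between the two sets of pairs. Replicate 2 exams exist in only one set, so a model without a pair term can take a difference between pairs for a difference between replicates, or let it cancel a real one.

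The score-model estimates are listed endpoints of a substudy meant to separate these sources of variation. If the model mixes them, the reported replicate shift or repeatability variance is partly something else, and the one interaction contrast that the design can estimate is not reported.

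**Working it through.** **1. The plan's counts.** 36 subjects give 72 eyes. 3 × 72 = 216 and 6 × 72 = 432, both as stated in SAP 5.2. Together they make 648 = 9 × 72, so the SAP counts belong to the A-I layout. The plan gives no figure for the overlap examined below.

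**2. What the layout can estimate.** Six cells give 5 degrees of freedom. Camera uses 2 and operator 2, which leaves 1: the contrast (A2 + B3 + C1) minus (A1 + B2 + C3). A full 3 × 3 table would have 4 interaction degrees of freedom. The other components fall on the camera and operator estimates because three cells are empty.

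**3. Replicate as a fixed effect, no pair term.** Camera + operator + replicate has rank 6. The least-squares replicate estimate is

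mean(C, F, H) − mean(A, B, D, E, G, I).

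Each eye has all nine exams, so a random eye or subject effect does not change these weights. Put +d in A-2, B-3, C-1 and −d in A-1, B-2, C-3, so the gap is 2d:

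bias = d − (3d − 3d)/6 = d, half the gap.

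**4. With a pair term.** The rank becomes 7 and the replicate estimate is the mean of C−B, F−E and H−G. The bias is d − d = 0.

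**5. Precision.** Assume 72 eyes and independent within-eye residuals with SD s.

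| Model | Variance factor per eye | SE |
|---|---|---|
| No pair term | 3/9 + 6/36 = 0.500 | √(0.500/72) s = 0.083s |
| Pair term | 6/9 = 0.667 | √(0.667/72) s = 0.096s |

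The SE ratio is √(0.667/0.500) = 1.155.

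**6. How much is absorbed.** Over the nine exams the pattern is +d six times and −d three times, and its mean is d/3 for every camera and operator. Its sum of squares after camera and operator is 9d² − 9(d/3)² = 8d². Replicate takes d²/0.500 = 2d², or 25%; the other 75% goes to the residual.

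**7. Replicate left out (SAP 5.2 list).** All 8d² per eye goes to the residual. Over 72 eyes that is 576d² on 648 − 72 − 4 = 572 degrees of freedom, so the residual variance rises by about d².

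**8. Range, under assumed gaps.**

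| Gap 2d | Replicate bias d | Bias / SE | Added residual variance if replicate is omitted |
|---|---|---|---|
| 0.10s | 0.05s | 0.6 | 0.0025s² |
| 0.25s | 0.125s | 1.5 | 0.016s² |
| 0.50s | 0.25s | 3.0 | 0.063s² |

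**9. Exam order.** Suppose the exams run A to I at positions 1 to 9. Set A = 1, B = 3, C = 7 for camera, 0, 1, 2 for operators 1, 2, 3, and add 1 for Replicate 2. The sums are 1, 2, 3, 4, 5, 6, 7, 8, 9. A linear sequence term is then an exact combination of camera, operator and replicate, and a pair term does not remove this. When order is randomised, the results in steps 3 and 4 also hold with a sequence term.

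**10. The table printed in 9.4.1.** With A-1, B-2 and C-3 only, the camera, operator and replicate columns have rank 5 of 7. Camera and operator are the same factor. Replicate is balanced over the pairs, so the mechanism in step 3 does not arise there.

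**The case against.** - **The SAP model has no replicate term, and the word additive appears nowhere.** True. Under that list no replicate effect can be biased; the contrast goes to the residual instead (step 7), which is a smaller effect. Protocol 8.1 and 9.4.1 do list a replicate effect, so the fixed-effect case cannot be set aside.
- **Repeatability is already assessed within pairs.** This stands for the agreement statistics (OA, APA, ANA, AUA), which cross-tabulate replicate 1 against replicate 2 and do not use the score model. For the algorithm score, however, SAP 5.2 assigns repeatability to the mixed model.
- **The sentence and the layout come from different sections.** Protocol 9.4.1 prints a table in which this problem does not occur. That is correct, but the A-I scheme stands in both documents and matches the SAP's counts, and the 9.4.1 table has the worse fault of merging camera with operator.
- **The size is hypothetical.** This stands. No document gives an interaction size, and no 5% test of a replicate effect is planned, so rejection rates for such a test would not describe this study.

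A reader might infer that any camera-by-operator interaction is reported as a replicate effect. The layout does not support that: only one of four interaction degrees of freedom can be separated, replicate takes 25% of its sum of squares, and other patterns load on camera or operator. One of four basis patterns tested gave zero replicate bias. Within-pair differences still separate replicate from the estimable contrast.

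**Conclusion.** The concern holds as a partial overlap in the nine-exam A-I layout. With a fixed replicate effect and no pair term, the replicate estimate is biased by exactly half the gap between the repeated and unrepeated pairs. With replicate omitted, the same contrast adds about d² to the residual variance, at most about 6% over the range shown. These results assume complete data, independent within-eye residuals, an interaction common to all eyes and an exam order not tied to the A-I listing. The gap itself is unknown, so the tabulated values are a range and not a prediction.

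The effect is confined to the score-model endpoints of the substudy. The co-primary sensitivity and specificity results and the agreement statistics are untouched. It is a worthwhile, inexpensive improvement and does not invalidate the substudy.

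**What to change.** Before changing the model:
1. Reconcile the protocol 9.4.1 table with the A-I layout in protocol 7.6 and 9.4 and SAP 3.2 and Supplementary Table 6.
2. Align the term lists in SAP 5.2, protocol 8.1 and protocol 9.4.1, and state whether replicate is a fixed effect or the residual component.
3. Vary exam order across subjects and print the scheme, so that sequence can be separated from camera, operator and replicate.

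Then, in SAP 5.2 and protocol 8.1 and 9.4.1, fit the six-level camera-operator pair: camera + operator + the contrast (A2 + B3 + C1) minus (A1 + B2 + C3). Report that contrast beside the camera and operator effects, and take the replicate effect from C−B, F−E and H−G. State that the remaining interaction components cannot be separated from camera and operator.

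The model change costs one degree of freedom, about 15% on the replicate standard error (0.083s to 0.096s) and some wording. It needs no extra exams. Varying the order requires an allocation scheme at the substudy sites.
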